## Abstract

**Background::**

Diabetes self-care activities, like, healthy diet, regular exercise, self-monitoring of blood glucose, and rational use of medicines are considered to play a vital role in establishing euglycemia. Health literacy among type 2 diabetes mellitus (T2DM) patients in Pakistan is very low, which is the most likely cause for poor clinical outcomes. This study is designed to investigate the impact of pharmacist-led educational intervention on glycemic control, self-care activities and disease knowledge among T2DM patients in Pakistan.

**Methods::**

In this randomized controlled trail, effectiveness of a 6-month pharmacist-led educational intervention will be examined on glycemic control, diabetes self-care activities and disease knowledge of 80 adult T2DM patients (age >30 years) with poorly controlled T2DM (HbA1c> 7%), after randomizing them into intervention and control groups, at diabetes care clinic of Capital Hospital Islamabad, Pakistan.

**Results::**

The primary outcome is change in patients’ HbA1c, whereas, changes in self-care activities and patients’ disease knowledge are the secondary outcomes. After baseline assessment of their self-care activities and disease knowledge by using validated Urdu versions of Diabetes Self-management Questionnaire (DSMQ) and Diabetes Knowledge Questionnaire (DKQ), respectively, interventional group patients will be supplemented with a face-to-face pharmacist-led educational intervention, whereas, the control group will receive usual care. Intervention arm patients will be educated successively at their first follow-up visit (12th week) and telephonically after every 4 weeks. All assessments will be made at baseline and end of trail for both intervention and control groups. Multivariate general linear model will be applied to analyze the effects of the intervention.

**Conclusion::**

Glycemic control in T2DM patients requires optimum self-care activities. This study is an attempt to improve self-care behaviors among poorly controlled T2DM patients who are at higher risk of diabetes-associated late complications.

## Introduction

1

Globally, diabetes has become a serious clinical and public health problem. According to World Health Organization (WHO), the diabetes number increased from 108 million in 1980 to 422 million in 2014.^[1]^ Diabetes is the leading cause of kidney failure, stroke, heart attack, blindness, and lower limb amputations, and when not properly managed, it will lead to higher health care cost, morbidity, and mortality, thereby creating greater financial burdens.^[2,3]^ With rapidly rising prevalence of diabetes, especially in the developing countries, it is projected to be the 7th leading cause of mortality in 2030.^[1,3]^ Worldwide approximately 415 million people have been diagnosed with diabetes mellitus (DM), and the number is expected to increase to 642 million by 2040,^[4]^ making it one of the leading noncommunicable health problem worldwide.^[5]^

Pakistan has been ranked 7th in diabetes disease burden in the world, it is projected to reach 15% by 2030, and if the present scenario continues, Pakistan is expected to move to top 4th place.^[6–8]^ According to the current statistics of International Diabetes Federation (IDF), in Pakistan there are 7.028 million cases of adults (20–79 years) with diabetes, with 6.9% prevalence rate and 2.928 million undiagnosed adults with diabetes.^[4]^

T2DM is the most prevalent (>90%) type of diabetes,^[9]^ requiring patients to adopt specific life style modifications in addition to continued pharmacotherapy. Because of the chronic nature of T2DM, diabetes self-care activities have become an integral component of effective diabetes care around the globe.^[10]^ Glycemic control, measured in terms of glycosylated hemoglobin (HbA1c), has been associated with significant reduction in diabetes-related complications and economic burden.^[11]^

T2DM is a self-managed, chronic metabolic disorder, where patients has to take major responsibility to manage their condition by adopting healthy self-care behaviors. The consequences of these self-care behaviors can directly affect health. Managing T2DM requires a huge amount of time, modifications in lifestyle, and confidence to do this. Because of the high cost associated with controlling diabetes, health care providers are now taking an active role in the provision education for diabetes self-management.^[12]^

Educational interventions can play an important role to improve patients’ knowledge and skills regarding diabetes self-management. Systematic reviews of interventions addressing diabetes self-management indicate that the diabetes education courses enhance knowledge, self-care behaviors, and reduction in HbA1C.^[13–16]^ Structured self-management education programmes can be delivered on a one-to-one basis or to groups of people with diabetes and should be facilitated by trained educators. The aim of the education is not only to improve knowledge and skills, but also to motivate a person to make and sustain lifestyle changes, by giving them the confidence to make their own treatment/lifestyle choices on a day-to-day basis.

Educational intervention on self-management can be delivered as group education or individually as one-to-one approach. Sturt et al. reported that an individualized approach with the help of a diabetes guide and telephonic support has demonstrated clinically significant reductions in A1c levels, for T2DM patients with poor glycemic control.^[17]^ Health literacy has been reported as a significant factor influencing the patients’ glycemic control.^[18]^ Clinical outcome can be achieved by addressing patients’ literacy. Pharmacist-based educational interventions are associated with improved medication adherence and glycemic control.^[19–21]^ A review of 16 pharmacist-based interventions resulted in an absolute reduction of HbA1c with an average of 0.62%.^[20]^ Similarly, in an another review, a reduction in A1c levels up to 2.1% was demonstrated by 20 pharmacist-based interventions.^[13]^ A study examining the effectiveness of a free rural clinic for diabetes patients managed by pharmacists found that patients who received education on diabetes, lifestyle modifications, and management of diabetes drug therapy had significant reductions in A1c (≥ 1%) after 24 months.^[22]^

Keeping in view the importance educational interventions in diabetes self-care and clinical outcomes, we designed a face-to-face short-term (6 months) pharmacist-led educational intervention model in poorly controlled T2DM patient (HbA1c >7%) in Pakistan. In this study, we will investigate the mean change in HbA1C at 6 months after the baseline, and a comparison will be made with a similar comparator group of T2DM patients receiving standard diabetes care. In addition, comparison between self-care activities and disease knowledge between the groups will also be studied.

## Methods

2

### Study design

2.1

This is a 24-week open label, parallel group, prospective randomized controlled trial. In this study, the impact of a pharmacist-based, face-to-face educational intervention will be investigated in adult Pakistani people with poorly controlled (HbA1c >7%) type 2 diabetes. The study flow is presented in (Fig. 1).

**Figure 1 F1:**
[figure not shown]
Study Flow Diagram.

### Study settings

2.2

This 6-month randomized controlled study will be conducted in a tertiary care diabetes care clinic of Capital Hospital (CDA), located in Islamabad, Pakistan. The recruitment and data collection will be performed between October 2017 and March 2018. Setting for pharmacist educational intervention in this study will be a private counselling room at CDA diabetes outpatient clinic.

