### Sample recruitment procedures

2.4

Patients will be identified from the hospital record and who will meet the inclusion criteria of the study will be invited telephonically for participation in the study. If the patient is willing to participate in the study, an appointment will be set in the outpatient counselling room of the pharmacist at CDA hospital and purpose of the study will be explained to the patient and his/her written informed consent will be obtained and baseline assessments will be done. Simple random sampling technique will be used from a list of random numbers of eligible patients which will be compiled by using the patients’ hospital identification numbers. After recruitment, the patients will be requested to handpick an envelope from the basket indicating allocation to either control or intervention group with 1:1 randomization. AB will generate the random allocation sequences, [name] will enrol participants and HS will assign participants to intervention and control groups.

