#### Primary aim

2.5.1

To investigate the effectiveness of a pharmacist-delivered diabetes management educational program on glycemic control (HbA1c) after completion of intervention (24th week).

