#### Study procedure

2.5.4

The participants will not be informed of their groups. After the initial assessment at baseline, the control group will receive usual care, whereas the interventional group will be provided with the structured intervention. A qualified pharmacist (researcher) will educate the patients in the interventional group about disease (diabetes), its symptoms, clinical goals, self-care activities (self-monitoring of blood glucose, physical activity, importance of regular medication in-take and healthy diet), and reducing risks, whereas the control group patients (N = 40) will receive the usual care.

The pharmacist will provide face-to-face diabetes management education (approximately 30 minutes duration) to the patients in the intervention group at their first visit, follow-up visit (12th week), and 4 telephone (4th, 8th, 16th, and 20th week) and will recommend physician visits when necessary. In addition to face-to-face educational intervention patients in the intervention group will also be provided informatory brochures about self-care activities, and a log book to keep record of their self-monitored blood glucose levels. The educational intervention and patient informatory material has been designed according to American diabetes Association (ADA) guidelines, the details of are presented in Table 1.

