**Table 1 T1:**
[figure not shown]
Module for educational intervention.

Details about patients’ (intervention and control group) demographics and lab profile (HbA1c, random blood sugar, fastening blood sugar, etc.) will be obtained by the pharmacist at first visit. At baseline and end of the trail (24th week), the diabetes disease knowledge and self-care activities of the patients in both groups (intervention and control) will be assessed by using 2 prevalidated questionnaires in Urdu language [24-item Urdu version of DKQ and 16-item Urdu version of DSMQ]. Pharmacists can assist the patient in completing questionnaires, but will not provide any help in answering the questions, as the same questionnaires will be used repeatedly. The details of study schedule for data collection are presented in Table 2.

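### The single October 2017 to March 2018 window leaves at most 14 days to enrol all 80 patients if each is to reach week 24 inside it

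*Protocol article*

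**What the plan says.** Section 2.2 (Study settings) gives the only calendar dates in the article: "The recruitment and data collection will be performed between October 2017 and March 2018". It sets no separate recruitment period and no later date for the end of follow-up.

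The per-patient duration appears in several places:

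- Section 2.1 (Study design): "This is a 24-week open label, parallel group, prospective randomized controlled trial".
- Section 2.5.1 (Primary aim) asks about the effect "on glycemic control (HbA1c) after completion of intervention (24th week".
- Section 2.5.4 (Study procedure), in the text after Table 1, times the secondary outcomes the same way: "At baseline and end of the trail (24th week), the diabetes disease knowledge and self-care activities of the patients in both groups".
- Section 2.2 also expresses the duration in months: "This 6-month randomized controlled study will be conducted in a tertiary care diabetes care clinic".

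Under section 2.4 (Sample recruitment procedures), patients are found in hospital records and those who qualify "will be invited telephonically for participation in the study". Each willing patient then attends an appointment in the pharmacist's counselling room for explanation, consent and baseline assessment, and draws an allocation envelope.

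**The concern.** When recruitment and outcome collection share one calendar window, its length must cover the recruitment period plus the full follow-up of the last patient. Here the window is barely longer than one patient's follow-up.

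The primary outcome is at stake. If the study team treats the end of March 2018 as a fixed close, late enrollees either have no week-24 HbA1c or are measured before week 24, with part of the 24-week programme undelivered. Both questionnaires are affected in the same way. If the team instead follows each patient to week 24, the data are safe but the published dates cannot be met. The article does not say which of the two governs.

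**Working it through.** **Inputs**

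- Window: October 2017 to March 2018 (section 2.2), read as generously as possible, from 1 October 2017 to 31 March 2018.
- Follow-up: 24 weeks = 24 × 7 = 168 days (sections 2.1, 2.5.1 and 2.5.4).
- Patients: 80 recruited, 40 per group, 62 evaluable required (sections 2.5.3 and 2.5.4).
- Sample-size assumptions: difference 1%, SD 1.4%, alpha 0.05 (taken as two-sided, since the article does not say), power 80% (section 2.5.3).

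**The plan's own figure**

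n per group = 2 × (1.96 + 0.8416)² × 1.4² / 1² = 30.8, rounded up to 31, so 62 in total. This matches section 2.5.3, and 62 is the benchmark used below.

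**Enrolment time on the 24-week reading**

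- Window: 31 + 30 + 31 + 31 + 28 + 31 = 182 days inclusive, or 181 days from first to last day.
- Days on which a patient can enrol and still reach week 24: 182 − 168 = 14.
- Last workable enrolment date: 31 March 2018 − 168 days = 14 October 2017.

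| Enrolled | Reaches week 24 | Inside window? |
|---|---|---|
| 1 October 2017 | 18 March 2018 | yes |
| 14 October 2017 | 31 March 2018 | yes, last day |
| 31 October 2017 | 17 April 2018 | no |
| 31 March 2018 | 15 September 2018 | no |

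**Enrolment time on the 6-month reading**

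1 October 2017 + 6 calendar months = 1 April 2018. Even a patient enrolled on the first day finishes as the window closes, so no recruitment time remains.

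**Workload of a 14-day intake**

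The days 1 to 14 October 2017 include 10 Monday-to-Friday days. 80 / 10 = 8 patients per weekday, each needing an appointment, consent, baseline assessment and allocation. Intervention patients also have a first education session of about 30 minutes: 40 × 30 minutes = 20 hours.

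**Tolerance if the end date is enforced**

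80 − 62 = 18. If more than 18 patients enrol after 14 October 2017, fewer than 62 can have a week-24 value in the window, even with no dropout. Those 18 places were added to cover attrition, so none is set aside for late enrolment.

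**Illustration only**

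Assume even enrolment of 80 patients from 1 October 2017 and a hard stop on 31 March 2018. Patients with a week-24 value = 80 × 14 / (days of recruitment). The article gives no enrolment pattern.

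| Recruitment lasts | Days | Patients with week 24 in window |
|---|---|---|
| 14 days | 14 | 80 (no loss) |
| 1 month | 31 | about 36 |
| 2 months | 61 | about 18 |
| 3 months | 92 | about 12 |
| 6 months | 182 | about 6 |

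**The case against.** The case on the other side has four parts.

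1. **The window is not strictly impossible.** A reader might infer that recruitment plus 24 weeks cannot fit at all. The documents do not support that. The contact schedule is in weeks, and on that reading 14 days remain. Section 2.4 samples from a compiled list of eligible hospital numbers, which is compatible with a fast batch intake, and about 8 patients per weekday is demanding but conceivable. This stands. Only the calendar-month reading leaves no time. But the article neither states nor plans a two-week intake, and it applies the same six-month window to recruitment.

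2. **Loss of the endpoint does not follow.** A reader might infer that most patients will lack the primary outcome or be measured early. Nothing in the article allows early measurement, and the outcome is tied to each patient's week 24. The team may simply keep that rule and let the dates slip, and then no data are lost. This stands, and the loss is therefore conditional on enforcing the end date.

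3. **The dates may cover only recruitment and baseline data.** That is possible, but the sentence names data collection without limit. If this was the intent, the wording still needs correcting.

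4. **The article is condensed, and Figure 1 and Table 2 are not visible here.** They may clarify the timing. However, the point is not about missing detail: the dates and the follow-up length are both stated, and they fit together only with an intake that the article does not describe.

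**Conclusion.** The point holds as a conflict between a stated calendar window and a stated follow-up, and it should be fixed. At most 14 days, 1 to 14 October 2017, are available to enrol all 80 patients if every week-24 assessment is to fall inside the window. None are available if follow-up means 6 calendar months. The 14-day figure assumes the widest possible window; a later start or earlier close shortens it.

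The consequence depends on which statement governs. If the end date does, each patient enrolled after 14 October 2017 lacks week-24 HbA1c, DKQ and DSMQ in the window, and more than 18 such patients take the trial below its required 62. If the week-24 rule does, the endpoint is intact and the published dates are wrong. No particular percentage of lost outcomes can be attributed to the plan: the counts by recruitment length rest on an assumed even enrolment, and the loss is nil if everyone enrols within 14 days. The endpoint definition, visit schedule and sample-size calculation are not themselves in error here.

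**What to change.** In section 2.2, replace the single window with two statements: a recruitment period with its own start and end dates, and an end of data collection defined as the week-24 assessment of the last randomised patient. If recruitment runs to 31 March 2018, that falls on about 15 September 2018. Add that week-24 measurements are not taken early to meet a calendar date.

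Alternatively, keep the March 2018 end and state that recruitment closes by 14 October 2017. This is credible only if the site can handle about 8 enrolments per weekday.

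The first option costs a short text amendment and a later closure, by up to the length of the recruitment period. Any other record carrying the same dates would need to match. The second option avoids the delay, but recruitment may stop short of 80.

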### Study population

2.3

Eligibility criteria for the study includes poorly controlled (HbA1c>7%) T2DM, adult patients (age ≥ 30 years) regardless of gender; speak and understand Urdu and / or English languages; having no significant comorbidity; being not involved in any trial/study related to diabetes during last 3 months and able to attend regular visits. Participants will be excluded if they are of other types of diabetes (gestational diabetes, T1DM); unable to answer the questionnaire independently or having hearing, vision, or cognitive impairments.

### Sample recruitment procedures

2.4

Patients will be identified from the hospital record and who will meet the inclusion criteria of the study will be invited telephonically for participation in the study. If the patient is willing to participate in the study, an appointment will be set in the outpatient counselling room of the pharmacist at CDA hospital and purpose of the study will be explained to the patient and his/her written informed consent will be obtained and baseline assessments will be done. Simple random sampling technique will be used from a list of random numbers of eligible patients which will be compiled by using the patients’ hospital identification numbers. After recruitment, the patients will be requested to handpick an envelope from the basket indicating allocation to either control or intervention group with 1:1 randomization. AB will generate the random allocation sequences, [name] will enrol participants and HS will assign participants to intervention and control groups.

### Study aims

2.5

#### Primary aim

2.5.1

To investigate the effectiveness of a pharmacist-delivered diabetes management educational program on glycemic control (HbA1c) after completion of intervention (24th week).

#### Secondary aim

2.5.2

To examine the impact of a pharmacist-delivered diabetes management educational program on self-care behaviors and patients’ diabetes knowledge, by using Urdu versions of 24-item Diabetes knowledge Questionnaire (DKQ) and 16-item Diabetes Self-management Questionnaire (DSMQ).

#### Sample size calculations

2.5.3

Study sample size is calculated based on previous studies ^[23–28]^ for detecting the difference of 1% reduction for HbA1C (effect size) with standard deviation of 1.4%, at 6 months in the intervention group. A significance level of 0.05 is considered with study power of 80%. Based on these numbers, the calculated sample size is 62 (31 for experimental group and 31 for controlled group); however, a sample of 80 patients is assumed to be sufficient to compensate for a 25% attrition rate.

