### Strengths and limitations

3.1

This interventional study is first of its kind to be conducted in Pakistan involving randomized control design. This study outcome will help to demonstrate the value of implementing a pharmacist-led educational intervention at diabetes care settings to improve self-care practices and clinical outcomes among Pakistani T2DM patients. A possible limitation of the study is the short duration (6 months intervention), which may not make it possible to examine intervention influence on diabetes related complications. Additionally, a 6-months intervention may result in high drop-out rate. To reduce the chances of drop-out, the researcher will facilitate patients in making appointments for follow-up assessment, and an additional 25% sample population will be recruited to compensate the drop-out.

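### Eighty patients cover up to 22.5% attrition, not the stated 25%: at 25% loss 60 remain, two below the protocol's own 62 (minor; power about 79%)

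*Protocol article*

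**What the plan says.** Section 2.5.3 of the protocol article (Sample size calculations) bases the size on "detecting the difference of 1% reduction for HbA1C (effect size"), "with standard deviation of 1.4"%, "at 6 months in the intervention group". It adds: "A significance level of 0.05 is considered with study power of 80"%. From these inputs it obtains 62 patients, 31 in each arm. It then moves to the recruitment target: "a sample of 80 patients is assumed to be sufficient to compensate for a 25% attrition rate".

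Section 3.1 (Strengths and limitations) notes that a six-month intervention may lead to many drop-outs. It describes help with follow-up appointments and says that "an additional 25% sample population will be recruited to compensate the drop-out".

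Section 2.4 sets 1:1 allocation and section 2.5.4 puts 40 patients in the control group, so the planned size is 40 per arm.

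**The concern.** Section 2.5.3 gives a required number, a recruitment target and a loss rate, and these three figures do not fit together. If a quarter of 80 patients are lost, fewer than 62 are left. The wording in section 3.1 suggests how this arose: 25% was added to the required number, which is not the same as allowing for the loss of 25% of those enrolled.

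What is at stake is the accuracy of a stated design property. A reader of section 2.5.3 would conclude that, at the attrition rate the protocol itself plans for, the primary HbA1c comparison still has the number of patients needed for 80% power. It falls slightly short.

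**Working it through.** **Inputs, all from the protocol article.** Difference 1.0 percentage point, SD 1.4 percentage points, alpha 0.05, power 80%, required number 62 (31 per arm), recruited number 80, attrition 25% (all section 2.5.3); 1:1 allocation (section 2.4).

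**Assumptions.** Section 2.5.3 does not say whether the test is one- or two-sided. I take it as two-sided because that reproduces 31 per arm; a one-sided 5% test would need only 25. I also assume equal losses in the two arms, except where stated.

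**Step 1: reproduce the required number.** By the normal approximation,

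n per arm = 2 × (1.960 + 0.8416)² × 1.4² / 1.0² = 2 × 7.849 × 1.96 = 30.77, rounded up to 31, so 62 in total. This matches the protocol exactly.

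**Step 2: apply the stated attrition.**

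- Remaining from 80 at 25% loss: 80 × 0.75 = 60, or 30 per arm. This is 2 below 62.
- Largest loss that still leaves 62: 1 − 62/80 = 22.5%.

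**Step 3: see where 80 comes from.**

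- Adding 25% to the requirement: 62 × 1.25 = 77.5, so 78. Eighty exceeds this.
- Dividing by the retained fraction: 62/0.75 = 82.7, so 83, or 84 with equal arms. Eighty falls short of this.

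**Step 4: power at the number remaining.** By the same normal approximation, power = Φ(1.0 / (1.4 × √(2/n)) − 1.960).

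- n = 31: Φ(2.812 − 1.960) = Φ(0.852) = 80.3%
- n = 30: Φ(2.766 − 1.960) = Φ(0.806) = 79.0%

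The non-central t distribution gives the power of a t-test (equivalently, a two-group ANOVA):

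| Per arm | Normal approximation | t-test |
|---|---|---|
| 30 | 79.0% | 77.6% |
| 31 | 80.3% | 79.0% |
| 32 | 81.5% | 80.3% |

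Moving from 31 to 30 per arm costs 1.3 points by the normal approximation and 1.4 points by the t-test.

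**Step 5: the same shortfall as a detectable difference.** By the normal approximation, 30 per arm has 80% power for 2.8016 × 1.4 × √(2/30) = 1.01 percentage points, against the target of 1.0.

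**Step 6: sensitivity to unequal losses.** If the 60 remaining were split 25 and 35, power would be Φ(1.0 / (1.4 × √(1/25 + 1/35)) − 1.960) = Φ(2.728 − 1.960) = 77.9%, or 76.5% by t-test.

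**The case against.** The strongest reply is that nothing of substance depends on this. Two evaluable patients and about 1.3 points of power are well within the uncertainty of a planning SD given to one decimal place. Sample size was chosen by a standard formula that reproduces exactly. The sentence in section 3.1 is true as written, because 80 is 29% above 62 (80/62 = 1.29). The protocol also plans measures to limit drop-out, and nothing in it shows that losses will exceed the 22.5% that 80 patients do cover. All of this stands, and it is why the point is minor. It does not make the sentence in section 2.5.3 correct, since that sentence names a 25% attrition rate and 80 patients do not cover it.

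Three stronger readings are tempting, and the document supports none of them.

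- **That attrition brings power from 80% down to 77.6%.** This compares a t-test figure with a target derived by the normal approximation. By t-test, power is already 79.0% at 31 per arm, so part of that gap is a change of formula and only about 1.4 points come from attrition.
- **That 31 per arm is itself an error because a t-test needs 32.** The normal approximation is a legitimate basis for planning, and one patient per arm is an approximation difference. Section 2.6.3 also allows rank-based tests and the abstract names a multivariate general linear model, so the protocol does not commit to a t-test alone.
- **That section 3.1 repeats a false statement.** It describes an addition to the sample, not a tolerated loss, and the addition is met. The risk is only that a reader takes it to mean that a 25% loss is covered.

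**Conclusion.** The attrition statement in section 2.5.3 is wrong as written, and the error is minor. The protocol's own figures leave 60 evaluable patients at 25% attrition, two short of its requirement of 62; full cover would take 84 with equal arms. The loss of power is small enough that no design decision turns on it, and the document does not support describing the trial as materially underpowered on this account.

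The shortfall in numbers rests on no assumption beyond the stated figures. The power figures rest on a two-sided 5% test and equal losses; a markedly uneven split of the same 60 patients would lower power by about another point.

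**What to change.** Keep the sample at 80 and restate the attrition sentence in section 2.5.3, for example: 'Recruiting 80 patients allows for up to 22.5% attrition while retaining 62. At 25% attrition, the 60 evaluable patients would give about 79% power for a 1% difference (normal approximation, two-sided 5% level, equal losses).' If the test was not planned as two-sided, the authors should say so, because 31 per arm would then not follow from the stated inputs.

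In section 3.1, align the wording with this, so that the added 25% is presented as an increase over the required number and not as cover for a 25% loss.

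The cost is two sentences, with no extra patients and no change in procedure. The stated tolerance becomes slightly less favourable. If the authors prefer to keep the claim of 25%, the alternative is to recruit 84 (42 per arm), four more than planned.
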